# The effect of passive mobilization associated with blood flow restriction and combined with electrical stimulation on cardiorespiratory safety, neuromuscular adaptations, physical function, and quality of life in comatose patients in an ICU: a randomized controlled clinical trial

**DOI:** 10.1186/s13063-021-05916-z

**Published:** 2021-12-30

**Keywords:** Blood flow restriction, Electrical stimulation, Cardiorespiratory safety, Intensive care unit-acquired atrophy, Intensive care unit-acquired weakness, Neuromuscular adaptations, Physical function, Quality of life, Critical care

## Abstract

**Background:**

Intensive care unit-acquired atrophy and weakness are associated with high mortality, a reduction in physical function, and quality of life. Passive mobilization (PM) and neuromuscular electrical stimulation were applied in comatose patients; however, evidence is inconclusive regarding atrophy and weakness prevention. Blood flow restriction (BFR) associated with PM (BFRp) or with electrical stimulation (BFRpE) was able to reduce atrophy and increase muscle mass in spinal cord-injured patients, respectively. Bulky venous return occurs after releasing BFR, which can cause unknown repercussions on the cardiovascular system. Hence, the aim of this study was to investigate the effect of BFRp and BFRpE on cardiovascular safety and applicability, neuromuscular adaptations, physical function, and quality of life in comatose patients in intensive care units (ICUs).

**Methods:**

Thirty-nine patients will be assessed at baseline (T0–18 h of coma) and randomly assigned to the PM (control group), BFRp, or BFRpE groups. The training protocol will be applied in both legs alternately, twice a day with a 4-h interval until coma awake, death, or ICU discharge. Cardiovascular safety and applicability will be evaluated at the first training session (T1). At T0 and 12 h after the last session (T2), muscle thickness and quality will be assessed. Global muscle strength and physical function will be assessed 12 h after T2 and ICU and hospital discharge for those who wake up from coma. Six and 12 months after hospital discharge, physical function and quality of life will be re-assessed.

**Discussion:**

In view of applicability, the data will be used to inform the design and sample size of a prospective trial to clarify the effect of BFRpE on preventing muscle atrophy and weakness and to exert the greatest beneficial effects on physical function and quality of life compared to BFRp in comatose patients in the ICU.

**Trial registration:**

Universal Trial Number (UTN) Registry UTN U1111-1241-4344. Retrospectively registered on 2 October 2019. Brazilian Clinical Trials Registry (ReBec) RBR-2qpyxf. Retrospectively registered on 21 January 2020, http://ensaiosclinicos.gov.br/rg/RBR-2qpyxf/

**Supplementary Information:**

The online version contains supplementary material available at 10.1186/s13063-021-05916-z.

## Background

Intensive care unit (ICU) therapies that are used to stabilize severe illnesses, such as sedatives, invasive access, and mechanical ventilation are responsible for prolonged lengths of bed restriction and, consequently, for reducing mobility in ICU [1–6]. In turn, mobility restriction is associated with losses in muscle mass and strength [4, 7–13].

ICU-acquired atrophy begins within the first 48 h of severe disease [14–16] and increases during the first two weeks of intensive care [15–17]. Studies suggest that severely ill patients may lose from 25 to 40% of peripheral muscle strength in two or more days of invasive mechanical ventilation [18–20]. During the first week of intensive care, there is evidence of associations between atrophy and weakness with high mortality rates [21–24] and, interestingly, even after discharge from the ICU with reduced physical function [25], higher functional dependence [26–28], and a reduction in quality of life [29–31].

Passive mobilization (PM) has been applied as a therapeutic strategy to reduce low mobility in patients unable to perform active exercises due to sedation [32] or non-induced comatose state [33], but without evidence of muscle atrophy and weakness prevention. Neuromuscular electrical stimulation [7, 8] is another strategy applied in critical care, involuntarily evoking muscle contractions through low-tension electric pulses [34]. Despite this, the efficacy of electrical stimulation still appears to be inconclusive, especially for severely ill patients [35, 36].

Barbalho et al. [37] investigated the use of blood flow restriction (BFR) associated with PM (BFRp) in comatose elderly patients in ICUs. This method consists of controlled mechanical compression to the muscle blood vessels through a pneumatic cuff [38], aiming to reduce arterial supply and muscle venous return and, consequently, stimulating muscle protein synthesis. In an intra-subject design study, both groups (PM and BFRp) presented muscle atrophy, although the application of BFR in one of the limbs efficiently reduced the loss of muscle mass. There were no adverse events, and the authors suggested BFRp as an effective strategy to reduce the magnitude of muscle mass loss.

Abe et al. [39] highlighted the intensity of exercise associated with BFR as an important aspect to optimize neuromuscular adaptations. Thus, Gorgey et al. [40] demonstrated a 17% increase in muscle mass after BFR combined with electrical stimulation in spinal cord-injured patients, compared to isolated electrical stimulation. Given the impossibility of performing active exercises, it seems also necessary to investigate the effects of BFR associated with PM and combined with electrical stimulation (BFRpE) in comatose patients to prevent muscle atrophy and weakness and possibly to optimize physical function and quality of life in ICU survivors.

Regarding BFR safety, after the release of between-sets BFR, rapid local muscular blood inflow and bulky venous return occur [41], which can lead to unknown repercussions in the cardiovascular system [42]. Consequently, these repercussions may reflect in critical changes in vital signs of severely ill patients and therefore in health recovery.

Hence, the present study aimed to investigate the effect of BFRp and BFRpE on cardiovascular safety and applicability, neuromuscular adaptations, physical function, and quality of life in ICU coma patients. We hypothesized that there will be no negative cardiovascular repercussions of BFRp, BFRpE, and BFRp will be able to reduce and BFRpE to prevent muscle atrophy and weakness, in addition to exerting more positive effects on physical function and on quality of life compared to BFRp.

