## Methods

### Primary objectives

The primary objectives are to investigate the effect of BFRp and BFRpE on cardiovascular safety in comatose patients in the ICU and to investigate the applicability of such protocols as early motor intervention methods in intensive care.

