##### Cardiovascular safety and applicability of peripheral muscle training

To assess cardiovascular safety, HR values < 50 bpm or > 180 bpm, SBP < 80 mmHg or > 160 mmHg, DBP < 60 mmHg or > 80 mmHg, MAP < 60 mmHg or > 120 mmHg, cardiac or respiratory arrythmias, SpO_2_ < 88%, signals of respiratory discomfort [50, 51], or signals of deep venous thrombosis will be considered criteria to interrupt the protocol. Except for the occurrence of deep venous thrombosis, two consecutive training attempts will be performed after the first training interruption before withdrawing the patient from the study. It is suggested for two main reasons: to exclude the possibility of an occasional adverse event due to the variability of the clinical conditions, and to maintain the training frequency in case the patient continues in the study. In case of exclusion, the protocol will be considered unsafe for this patient. However, in case 15% or more unsafe conditions occur in the same training protocol, the protocol will be excluded from the study. To evaluate the applicability, the number of adverse events and intercurrence will be recorded, and if a total number of adverse events and/or intercurrence overcome 20% of the total training sessions, or there is deep venous thrombosis occurrence in at least 5% of the patients, protocols will be considered unsafe and impracticable. If cardiovascular variations are greater than 20% of the baseline, the protocol will be considered impractical.

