### Quality of life assessment

#### Quality of life using the SF-36 questionnaire

Quality of life will be assessed using the SF-36 questionnaire, an instrument of good acceptance, reliability, and validity for ICU patients validated in Brazil and easily administered by telephone [45, 46, 53, 54]. It comprises 8 domains: physical function, role-physical, bodily pain, general health, vitality, social functioning, role-emotional, and mental health. Scores range from 0 to 100, where 0 corresponds to the worst general health status, and 100 corresponds to the best health condition [86–88]. The categorization and description of the methods and analyses are shown in Table 2.

**Table 2 Tab2:** Categorization and description of the methods and analyses of the study variables

Evaluation category	Organic responses	Method of evaluation	Variables in analyses
Safety and applicability	Acute cardiovascular	Pulse wave analysis (PWA)	MAP, SBPc, SBPp, DBPc, and DBPp (mmHg)
Safety and applicability	Acute cardiovascular	Analyses of the vital signs	HR (bpm) and SpO_2_ (%)
Muscle systems	Muscle mass adaptation	Ultrasound image	Muscle thickness (cm)
Muscle systems	Muscle quality adaptation	Ultrasound image	Echo intensity (A. U. from 0 to 256)
Neuromuscular systems	Global muscle strength adaptations	Medical Research Council (MRC) Score	Number scoring (0 to 60)
Physical function	Adaptations in physical function in ICU	Physical Function in the Intensive Care Test Scored (PFIT)	Number scoring (0 to 12)
Physical function	Adaptations in physical functional performance after hospital discharge	Performance in the basic activities of daily living by the Barthel Index (BI) by telephone interview	Number scoring (0 to 100)
Clinical outcomes	Adaptations in quality of life	Medical Outcome Study 36 – Item Short Form Health Survey (SF-36) questionnaire	Number scoring (0 to 100)

*SBPc* central systolic blood pressure, *SBPp* peripheral systolic blood pressure, *DBPc* central diastolic blood pressure, *DBPp* peripheral diastolic blood pressure, HR heart rate, *MAP* mean arterial pressure, *SpO*_*2*_ peripheral oxygen saturation, *ICU* intensive care unit

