## Statistical analysis

After data collection, participants will be distributed into subgroups by periods in coma (2, 3–4, 5–6 days), in alertness (1–2, 3–4, 5–6 days), and in ICU permanence (3–4, 5–6, 7–8, 9–10, 11–12 days). The normality of data will be analyzed using the Shapiro-Wilk test. One-way analysis of variance (ANOVA) will be used for intra-group comparisons in T0. A mixed-model analysis will be used for each dependent variable, whereas group and time will be considered as fixed factors and subject as the random factor. In case of significant *F*, the Tukey adjustment will be applied for multiple comparisons. In the event of a non-normal data distribution, a Kruskal-Wallis test will be applied to test for the differences in baseline values and the Friedman test to analyze the repeated measures. The adjusted *p* values will be calculated using the Hommel procedure [48]. Effect sizes between and within groups will be calculated using Cohen’s *d* [89]. The minimal clinically important difference will be assessed with distribution-based methods [90]. The statistical significance will be assessed at *p* < 0.05. All analyses will be performed using R 3.6.2 (The R Project for Statistical Computing, 2019) in R-studio 1.3.443 (RStudio Inc., Boston, MA, USA).

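### The no-harm hypothesis on cardiovascular safety is tested only by a difference test at p < 0.05 with 10 to 13 patients per arm, so a non-significant result cannot support it

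*Protocol article*

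**What the plan says.** The Primary objectives section reads "The primary objectives are to investigate the effect of BFRp and BFRpE on cardiovascular safety in comatose patients in the ICU", and adds applicability. At the end of the Background the expectation is put as an absence of harm: "We hypothesized that there will be no negative cardiovascular repercussions of BFRp, BFRpE". The text does not label this hypothesis primary, but the objective it belongs to is.

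Table 2 lists the variables analysed for safety and applicability: mean arterial pressure (MAP), central and peripheral systolic and diastolic pressure, heart rate and SpO2. That makes seven.

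The Statistical analysis section covers them with one general sentence, "A mixed-model analysis will be used for each dependent variable, whereas group and time will be considered as fixed factors", followed by "In case of significant *F*, the Tukey adjustment will be applied for multiple comparisons" and "The statistical significance will be assessed at *p* < 0.05". For non-normal data it substitutes rank-based difference tests. It also plans Cohen's d between and within groups, without an interval.

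The section on cardiovascular safety and applicability sets separate rules:
- vital-sign limits that interrupt a session;
- unsafe status for a patient who is excluded after repeat attempts;
- removal of a training protocol at 15% or more unsafe conditions;
- a verdict of unsafe and impracticable if adverse events exceed 20% of sessions or deep venous thrombosis reaches 5% of patients;
- "If cardiovascular variations are greater than 20% of the baseline, the protocol will be considered impractical".

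The Statistical analysis section does not refer to any of these rules.

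**The concern.** The hypothesis is that there is no harm, and the null hypothesis of the planned test is also that there is no difference. Within the Statistical analysis section, the hypothesis can be supported only by failing to reject. A small trial fails to reject easily, whatever the truth. Making the arm contrasts conditional on F and then adjusting them guards against false claims of benefit. Applied to a safety question, it makes a harmful difference harder to show.

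The Background calls the circulatory consequences of cuff release unknown and says that they may bring critical changes in vital signs. The Abstract says that the data will inform the design of a later trial. What that trial's designers need from this one is how large a BFR-versus-PM difference remains compatible with the data. A p value does not show that, and neither does a Cohen's d without an interval.

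**Working it through.** **Inputs.** The Sample size rationale gives 30 patients as the basis and 39 to be recruited. With equal allocation (assumed, as no ratio is stated) this is n = 10 or 13 per arm. A 10% loss from 39 leaves 35.1, or 11.7 per arm, which lies inside that range. Alpha is 0.05, taken as two-sided because the text does not say. The article states no effect size, SD or power for the cardiovascular variables, so there is no power figure of its own to reproduce. Differences are therefore expressed in SD units (d).

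**Power of one BFR-versus-PM comparison.** The test is an exact noncentral t with noncentrality d·√(n/2).
- Unadjusted: df = 2n − 2, critical value 2.101 (n = 10) or 2.064 (n = 13).
- Tukey for three arms: df = 3n − 3, critical value q/√2 = 2.479 or 2.444.
- For d = 0.5 the noncentrality is 0.5·√5 = 1.118 or 0.5·√6.5 = 1.275. Power is 0.185 or 0.232 unadjusted, and 0.102 or 0.134 with Tukey.

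| True difference | Missed, unadjusted (n = 10 / 13) | Missed, Tukey (n = 10 / 13) |
|---|---|---|
| 0.5 SD | 81% / 77% | 90% / 87% |
| 0.8 SD | 60% / 50% | 74% / 65% |
| 1.0 SD | 44% / 31% | 58% / 45% |

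**Repeated measures.** These figures ignore any precision gained from measuring each patient at rest, during exercise and afterwards. A simulation (20,000 runs) of the group-by-time F test, with a 0.5-SD shift at the exercise time only, gave misses of about 77–83% at an assumed within-patient correlation of 0.5 and 57–67% at 0.75. The gain is real but does not change the conclusion.

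**Interval width.** The 95% half-width for an arm difference in change from rest is t·√(2/n) in SDs of the change score. That is 2.101·√(2/10) = 0.94 SD at n = 10 and 2.064·√(2/13) = 0.81 SD at n = 13. An observed difference of zero would therefore leave harms of 0.8 to 0.9 SD open.

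**Do the separate safety rules fill the gap?** Reading the 15% rule as the proportion of patients classed unsafe in an arm, it triggers at 2 patients or more, since 1/10 = 10% and 1/13 = 7.7% fall below it. By exact binomial:
- a true 30% unsafe rate is flagged 85% (n = 10) or 94% (n = 13) of the time;
- a true 20% rate is flagged 62% or 77%, so it passes 38% or 23% of the time.

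With no unsafe patients, the one-sided 95% upper bound is 1 − 0.05^(1/n), which is 26% at n = 10 and 21% at n = 13. Both exceed the 15% limit. None of the rules compares a BFR arm with PM.

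**The case against.** **Non-significance is nowhere equated with safety.** A reader might infer that a relevant harm would usually be read as safety. The documents do not support that. The article judges safety and applicability by limits fixed in advance, and those limits would catch a large harm. This stands, and it confines the point to what the significance test can and cannot show.

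**The miss rates depend on the size of harm chosen.** The article's only limit on cardiovascular change is 20% of baseline. Assume a resting MAP of 85 mmHg, so 20% is 17 mmHg, and SDs of change of 8, 12 and 16 mmHg. A shift of that size is then 2.1, 1.4 or 1.1 SD. At 10 to 13 per arm it is detected 99–100%, 85–93% or 61–74% of the time unadjusted, and 98.5–99.8%, 75–87% or 47–61% with Tukey. So a harm as large as that limit would usually be seen, about evenly at the largest SD with Tukey. This stands too: the weakness concerns moderate differences, and the SD is not given.

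**Estimates do not vanish when F is non-significant.** A reader might infer that they do, but Cohen's d between groups is planned without that condition. What is missing is an interval around it.

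**Hommel.** A reader might take the sentence "values will be calculated using the Hommel procedure" to mean a correction across all seven variables. It follows the rank-test fallback and does not state its scope, so no figure here relies on that reading.

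**Pilot status.** Low power is expected in a pilot, and interval reporting is often left to an analysis plan. But the article does fix its method, and that method cannot answer its stated hypothesis. Pilot status argues for estimation with intervals rather than a significance test.

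**Conclusion.** The point holds in a limited form. The hypothesis of no negative cardiovascular repercussions has no matching inference: a difference test at this sample size misses a 0.5-SD BFR-versus-PM difference 77–81% of the time (87–90% with Tukey) and a 1-SD difference 31–44% (45–58% with Tukey). A non-significant result cannot support the hypothesis. The separate rules are real safeguards against large harms, but they carry no confidence bounds and make no comparison with the control arm.

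The figures assume equal allocation, a two-sided test and independent groups with one value per patient. High within-patient correlation would lower the miss rates, but at a correlation of 0.75 they still exceed one half for a 0.5-SD shift. This should be changed before analysis. It does not show that the trial would declare an unsafe protocol safe.

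**What to change.** In the Statistical analysis section, take the T1 cardiovascular variables out of the path that makes arm contrasts depend on a significant F.
- For each variable, always report the BFRp-minus-PM and BFRpE-minus-PM differences in change from rest, with unadjusted 95% confidence intervals from the same mixed model.
- Beside the existing safety limits, report the proportion of unsafe patients in each arm with an exact confidence interval.
- State that p > 0.05 will not be read as evidence of safety, and that wide intervals will be reported as inconclusive.

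Do not turn the 20%-of-baseline limit into a between-arm margin for all variables. It is written as a limit on change from baseline with the label impractical, and it does not suit SpO2. On an assumed resting SpO2 of 95%, 20% is 19 points, so a fall to 76% would be accepted, well below the article's own 88% interruption limit. If a margin is wanted, the investigators should pre-specify one per variable, consistent with the limits already in the safety section.

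The cost is a few sentences, with no new patients or measurements. The downside is that some variables will be reported as inconclusive rather than as showing no effect.

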### Secondary objective

The secondary objective is to investigate the effects of this intervention on neuromuscular adaptations, physical function, and quality of life of ICU coma-surviving patients.

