### Study design

This study describes a protocol for a pilot study of a double-blind, randomized controlled clinical trial of applicability and intervention, with transverse temporality and a three-arm factorial intervention design in accordance with the Standard Protocol Items: Recommendations for Interventional Trials (SPIRIT) guidelines*.* The SPIRIT verification list can be found in the Additional File 1 and is represented in Fig. 1. The flowchart for the clinical trial is shown in Fig. 2.

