### Sample size rationale

A total of 30 participants were used for the sample size calculation of the clinical trial [43]. Therefore, a sample of 39 patients will enable 10% sample loss for each experimental group (PM/control, BFRp, and BFRpE). Based on a recruitment average of 24 patients per month, 20% of non-consent and 30% of non-previewed death or immediate discharge, we aimed to recruit 7.2 patients per month. The recruitment in a single ICU will allow the study to be completed in a minimal period of 6 months.

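### The hypothesis is that BFRpE will prevent atrophy, but the stated difference tests could not support a no-loss conclusion with about 10 to 13 patients per arm

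*Protocol article*

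**What the plan says.** The Background of the protocol article ends with the hypothesis that "BFRp will be able to reduce and BFRpE to prevent muscle atrophy and weakness". The article's Discussion repeats the split: the first BFR protocol is meant to reduce atrophy and weakness, and the one with electrical stimulation is meant to prevent them. The Background also reports that in the earlier within-patient study both conditions lost muscle and BFR only lessened the loss. *Prevent* is therefore a different and stronger claim than *reduce*.

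The Statistical analysis section plans a mixed model for each dependent variable, with group and time as fixed factors and subject as random factor. It adds Tukey comparisons after a significant F, Hommel-adjusted p values and a 0.05 threshold. If data are not normal, Kruskal-Wallis is assigned to baseline differences and Friedman to the repeated measures. Two further yardsticks are listed: "Effect sizes between and within groups will be calculated" with Cohen's d, and "The minimal clinically important difference will be assessed with distribution-based methods". Neither is linked to the prevention hypothesis.

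On status, the Study design section states "This study describes a protocol for a pilot study of a double-blind, randomized controlled clinical trial". The Secondary objective section places muscle outcomes second: "The secondary objective is to investigate the effects of this intervention on neuromuscular adaptations, physical function, and quality of life". The Discussion paragraph of the Abstract says "the data will be used to inform the design and sample size of a prospective trial to clarify the effect of BFRpE on preventing" atrophy and weakness.

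**The concern.** A difference test can show that muscle was lost. It cannot show that none was lost, because a non-significant result may only reflect few patients or noisy measurement. A no-loss statement needs an interval that rules out a loss large enough to matter, and the plan attaches no such rule to *prevent*.

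The stated tests also lean towards within-arm change. With group and time as main effects only, neither term compares the change in one arm with the change in another; that is the group-by-time term, which is not named. In the non-normal branch, Friedman compares times within patients and has no between-arm component, and Kruskal-Wallis is reserved for T0. In that branch no named test compares the arms on change. The easy reading of such output is that PM changed significantly and BFRpE did not, which is not a test of BFRpE against PM.

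At stake is the signal on muscle thickness that goes into the planning of the later trial.

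**Working it through.** **Arm size.** The Sample size rationale gives "A total of 30 participants were used for the sample size calculation of the clinical trial" and "a sample of 39 patients will enable 10% sample loss for each experimental group". No allocation ratio is stated. With equal arms, 30/3 = 10 and 39/3 = 13.

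The step from 30 to 39 does not reproduce with 10% loss. 30/0.9 = 33.3, so 34 in total; per arm 10/0.9 = 11.1, so 12, or 36 in total. 39 appears only as 30 × 1.30. That is a separate matter; n = 10 and n = 13 are used here as the two ends.

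**Assumptions.** The documents give no SD, expected loss, power or no-loss margin for muscle thickness. The true loss d is therefore an assumed range, in SDs of the within-patient change from T0 to T2. Tests are taken as two-sided at 0.05.

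**Chance of missing a real loss.** For an unadjusted paired t test within one arm, P(non-significant) = F(t₀.₉₇₅,ₙ₋₁; n−1, d√n), where F is the noncentral t distribution function. At d = 0.5 the noncentrality is 0.5√10 = 1.58 (n = 10) or 0.5√13 = 1.80 (n = 13), giving 0.707 and 0.618.

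**Chance of the misleading pattern.** If PM and BFRpE lose the same amount, P(PM significant, BFRpE not) = power × (1 − power). At d = 0.5 this is 0.293 × 0.707 = 0.207 (n = 10) and 0.382 × 0.618 = 0.236 (n = 13). The product cannot exceed 0.5 × 0.5 = 0.25.

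The Tukey columns come from a simulation of 20,000 trials with three arms of identical loss, pooled error and six group-by-time cells. Each cell shows n = 10 / n = 13.

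| True loss (SD of change) | Loss missed, unadjusted | Loss missed, Tukey | PM significant, BFRpE not, unadjusted | Same, Tukey |
|---|---|---|---|---|
| 0.3 | 86% / 83% | 97% / 96% | 12% / 14% | 2% / 3% |
| 0.5 | 71% / 62% | 91% / 87% | 21% / 24% | 8% / 11% |
| 0.8 | 38% / 25% | 68% / 54% | 24% / 19% | 20% / 23% |
| 1.0 | 20% / 9% | 46% / 28% | 16% / 8% | 23% / 19% |
| 1.5 | 1.3% / 0.1% | 6% / 1% | 1.3% / 0.1% | 5% / 1% |

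In the same simulations, an unadjusted direct comparison of change between PM and BFRpE was falsely significant in about 5% of trials at every loss.

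**What an interval rule would do.** The 95% half-width for a within-arm mean change is t₀.₉₇₅,ₙ₋₁/√n = 0.72 SD (n = 10) or 0.60 SD (n = 13). Suppose *prevent* requires the lower limit to lie above −M. An arm truly losing M is then called prevented 2.5% of the time. If the true loss is zero, the chance of meeting the rule at n = 10 / 13 is 29% / 38% for M = 0.5 SD, 62% / 75% for 0.8 SD and 80% / 91% for 1.0 SD. M is again an assumption.

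**The case against.** The strongest reply is that this is a pilot whose primary objectives are cardiovascular safety and applicability. Muscle thickness is secondary, and the Abstract leaves clarifying the effect on prevention to a later trial. A margin for a secondary hypothesis may well sit in an analysis plan that is not shown, and a condensed article may simply not spell out an interaction term.

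Much of this stands. It limits the severity, and the absence of a margin alone would not be a finding. What remains is a mismatch within the article: it states the hypothesis, the tests and the threshold, and the non-normal branch it names has no between-arm test of change.

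Four stronger readings are tempting, and the documents do not support them:

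- A reader might infer that p < 0.05 on the time comparison is the only criterion. Group is also a fixed factor, and Cohen's d and an MCID are planned.
- A reader might infer that the investigators will declare prevention from a non-significant change. No section states that rule.
- A reader might infer that smaller arms and multiplicity adjustment always make a false prevention signal more likely. They do raise the chance that a single arm's loss is missed. The pattern of PM significant and BFRpE not moves either way: at 0.5 SD it is lower with 10 patients than with 13 and lower with Tukey, while at 1.0 SD both comparisons reverse.
- A reader might infer that the pilot will pass on prevention as an established result. The Abstract says its data will inform design and sample size.

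The two-point calculation also ignores the daily thickness measurements, which could make the mixed model more precise than shown.

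**Conclusion.** The concern holds in this limited form: as written, the analysis cannot support *prevent*, and a non-significant T0 to T2 change in about 10 to 13 BFRpE patients should not be read that way.

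How much this matters depends on a loss the documents do not give. Missing a real loss is likely at 0.3 to 0.5 SD of the change score, still appreciable at 0.8 SD, and nearly absent at 1.5 SD without adjustment. With equal loss in both arms, the misleading contrast of significance can arise in up to about 25% of trials, against about 5% for a direct between-arm test. These figures assume equal arms, independent patients and normally distributed change scores. Because the outcome is secondary in a pilot, the severity is minor to moderate.

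**What to change.** In the Statistical analysis section, state three things:

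1. Conclusions on muscle thickness rest on the between-arm contrasts of change from T0 (the group-by-time term: BFRp against PM, BFRpE against PM, BFRpE against BFRp), each with a 95% confidence interval. The same applies if data are non-normal, for example through a between-arm comparison of change scores in place of Friedman alone.
2. A non-significant within-arm change is reported as loss not excluded.
3. *Prevent* is used only if the interval for the BFRpE change also excludes a loss as large as the planned MCID, with its value fixed before unblinding and expressed in the same units as the change.

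The cost is wording; the data are already to be collected. The downside is low power. Between-arm power (normal approximation, unadjusted) for a difference of 0.5, 0.8 or 1.0 SD is about 20%, 43% or 61% with 10 per arm and 25%, 53% or 72% with 13. With a tight margin, prevention would rarely be shown even if true, which fits leaving that question to the later trial. The third item is optional; the first two carry most of the benefit.
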